#### 6.5.1 Observation, inspection and investigation details

The principal investigator or clinical trial co-investigator will investigate and record the following items.

##### (1) Subject background

###### [Investigation items]

Subject identification code, date of consent, sex, date of birth, age, height, weight, primary disease (disease causing lower limb ischemia), lower limb targeted for biotube transplantation (hereafter referred to as the "target lower limb"), evaluation of the target lower limb, medical history (those cured at the time of eligibility confirmation) and presence or absence of complications (those not cured at the time of eligibility confirmation), and their details, pregnancy test, nutritional status, and status of the site where the test device is to be implanted.

###### [Survey period]

At the time of confirming eligibility

###### [Survey method]

The survey will be conducted through interviews and examinations. If it is difficult to measure height using a height gauge due to the subject being unable to maintain an upright position, simple measurements using a tape measure will be accepted. If the subject is a woman of childbearing potential, a pregnancy test will be conducted to confirm that she is not pregnant (the method of testing is not required).

###### [CRF contents]

Subject identification code, consent acquisition date, sex, date of birth, age (at the time of consent acquisition), date of height measurement, height [cm] (integer: rounded to the nearest tenth), date of weight measurement, weight [kg] (to the nearest tenth: rounded to the nearest tenth), primary disease, target limb (right or left), evaluation of target limb (presence or absence of history of revascularization including endovascular treatment and details thereof, presence or absence of amputation and details thereof, length of biotube required for bypass surgery), medical history, presence or absence of complications and disease name, pregnancy test (whether or not it was performed, date of test, result of test, reason for not performing it), nutritional status (CONUT score), status of planned site for implantation of the study device (planned site, planned site for implantation, details of abnormality including skin abnormality)

##### (2) Subjective and objective findings

###### [Survey items]

Subjective and objective findings (findings associated with severe limb ischemia: pain, numbness, heat, tenderness, swelling, wounds, exudate, ulcers/erosions, fever, and other notable findings)

[Survey period]

At the time of eligibility confirmation, Visit 2 (before implantation of the test device), Visit 5, Visit 6 (before removal of the test device), Visit 7 (before implantation of the biotube), Visit 8, Visit 9, Visit 10, Visit 11, Visit 12, Visit 13, and at the time of discontinuation

[Survey method]

Confirm by examining the patient. Also, take a photograph of any wounds caused by the primary disease.

[CRF contents]

Presence or absence of subjective and objective findings and abnormalities associated with severe lower limb ischemia: presence or absence of pain, numbness, heat sensation, tenderness, swelling, wounds, exudate, ulcer/erosion formation, fever (37.5°C or higher within 24 hours), and other notable findings) and their details [including size (length and width) for wounds], presence or absence of photograph of wound site, date of photograph, photograph of wound site (if there is a wound)

(3) Vital signs

[Survey items]

Temperature, blood pressure, pulse rate

[Survey period]

At the time of eligibility confirmation, Visit 2 (before implantation of the test device), Visit 5, Visit 6 (before removal of the test device), Visit 7 (before implantation of the biotube), Visit 8, Visit 9, Visit 10, Visit 11, Visit 12, Visit 13, at the time of discontinuation

[CRF contents]

Temperature [°C] (to one decimal place), blood pressure (systolic and diastolic) [mm Hg] (integer), pulse rate [beats/min]

(4) Blood tests (hematological tests, blood biochemistry tests, blood coagulation tests)

[Survey items]

1. Hematological tests: white blood cell count (differential), red blood cell count, hemoglobin content, hematocrit value, platelet count, total lymphocyte count (only at the time of eligibility confirmation)
2. Blood biochemistry tests: total protein, albumin, fasting blood glucose, AST (GOT), A triglyceride, LDL cholesterol, LDH, BUN, creatinine, Na, K, Cl, CRP, total cholesterol (only at the time of eligibility confirmation)
3. Blood coagulation tests: PT, PT-INR, APTT

[Survey period]

At the time of eligibility confirmation, Visit 2 (before implantation of the test device), Visit 5, Visit 6 (before removal of the test device), Visit 7 (before implantation of the biotube), Visit 8, Visit 9, Visit 10, Visit 11, Visit 12, Visit 13, at the time of discontinuation

[CRF contents]

Each test value

(5) Lower limb arterial echocardiography

[Survey items]

Lower limb arterial echocardiography

[Survey period]

At the time of eligibility confirmation, Visit 5, Visit 10, Visit 11, Visit 12, Visit 13, and at the time of discontinuation

[CRF contents]

Arterial echocardiography findings of the target lower limb [presence or absence of infarction or stenosis in the artery of the target lower limb, presence or absence of new infarction or stenosis in the artery of the target lower limb (findings, presence or absence of abnormal findings)], diameter and presence or absence of stenosis of bypass graft after transplantation (findings, presence or absence of abnormal findings)

(6) Upper and lower limb venous ultrasound examination

[Survey items]

Upper and lower limb venous ultrasound examination

[Survey period]

At the time of eligibility confirmation (for dialysis patients, upper limb examination is not necessary)

[CRF contents]

Upper and lower limb venous ultrasound examination findings (location, length and presence or absence of varicose veins, presence or absence of autologous veins that can be used for arterial bypass surgery)

(7) Lower limb CT angiography, lower limb arteriography

[Survey items]

Lower limb CT angiography, lower limb arteriography

[Survey period]

At the time of eligibility confirmation, Visit 10, Visit 13 (performed if possible)

[Survey method]

Perform lower limb CT angiography and/or lower limb arteriography for the target lower limb.

[CRF contents]

Test method, presence or absence of findings related to ischemia in the target lower limb, and findings

(8) Lower limb X-ray examination

[Survey items]

Lower limb X-ray examination

[Survey period]

At the time of eligibility confirmation, Visit 10, Visit 11, Visit 12, Visit 13, and at the time of discontinuation

[CRF contents]

Presence or absence of X-ray findings of the target lower limb, findings, and presence or absence of osteomyelitis

(9) ABI (Ankle Brachial Index) Test

[Survey items]

ABI Test

[Survey period]

At the time of eligibility confirmation, Visit 10, Visit 11, Visit 12, Visit 13, and at the time of discontinuation

[CRF contents]

ABI measurement values (right, left)

(10) SPP (skin perfusion pressure) test

[Survey items]

SPP test

[Survey period]

At time of eligibility, Visit 10, Visit 11, Visit 12, Visit 13, and at time of discontinuation

[CRF contents]

SPP of target limb [mm Hg] (integer)

(11) Ischemic state evaluation

[Survey items]

Scores in each category of Wifl and GLASS classification

[Survey period]

Wifl classification: At the time of eligibility confirmation, Visit 10, Visit 11, Visit 12, Visit 13, at the time of discontinuation

GLASS classification: At the time of eligibility confirmation

[CRF content]

Scores in each category of Wifl and GLASS classification for the target limb

(12) Lower limb MRI examination

[Survey item]

Lower limb MRI examination

[Survey time]

At the time of eligibility confirmation (performed if osteomyelitis is suspected in the target lower limb and examination is possible)

[CRF content]

Presence or absence of MRI examination of the target lower limb and findings, presence or absence of osteomyelitis

(13) Eligibility check by a third party

[Survey item]

Status of eligibility check by a third party

[Survey period]

At the time of eligibility confirmation

[CRF contents]

Whether or not a third-party eligibility check was conducted and the details (including the date and person who checked)

- (14)        Implantation of the test device
- [Survey item]
- Compliance with the implantation procedure of the test device
- [Survey period]
- Visit 2
- [Survey method]
- Investigate compliance with "6.4.2 Procedures for using the test device BTM1".
- [CRF content]
- Compliance with the implantation procedure of the test device (number of implants and location (including left and right), size)
- 
- (15)        Echo examination of the test device implantation site (including break drain removal)
- [Survey item]
- Echo examination of the test device implantation site
- [Survey period]
- Visit 3 (before break drain removal), Visit 4
- [Survey method]
- Conduct an ultrasound examination before and approximately one week after the break drain removal to confirm the presence or absence of blood or exudate at the test device implantation site.
- [CRF content]
- Echo examination findings at the test device implantation site (presence or absence of blood or exudate, BTM1 number with findings, including the date of break drain removal)
- 
- (16)        Questionnaire survey
- [Survey items]
- Details regarding implantation of the test device and QOL after biotube implantation
- [Survey period]
- Visit 5, Visit 13, and at the time of discontinuation
- [Survey method]
- A questionnaire survey was conducted on subjects after removal of the test device and 12 weeks after implantation of the biotube.

[CRF contents]

Before implantation of the test device (anxiety and expectations regarding the treatment of implanting the test device, about creating one's own blood vessels in one's own body, other opinions), after implantation of the test device (discomfort and anxiety at the time of implantation, presence or absence of pain such as pain and itching, impact on daily life and inconvenience, difference from imagination before implantation, change in feelings about the device during the implantation period, discomfort and anxiety after removal, other opinions), after implantation (condition of the implanted area, pain and itching at the implanted area, wound pain and improvement in walking, impact on daily life, other opinions)

(17) Removal of the test device

[Survey item]

Compliance with the removal procedure of the test device

[Survey period] Visit 6

[Survey method]

Investigate compliance with "6.4.2 Procedure for using the test device BTM1".

[CRF description]

Compliance with the removal procedure of the test device (formation of subcutaneous hematoma, accumulation of subcutaneous exudate, excessive adhesion, infection, rust, disintegration, damage of BTM1, deterioration and damage of the internal core)

(18) Quality evaluation of biotubes (including preservation of samples for histopathological evaluation of biotubes)

[Survey items]

Information on quality evaluation of biotubes and preservation of samples for histopathological evaluation

[Survey period] Visit 6, Visit 7 (performed if necessary) (see "6.4.2 Procedures for using the test device BTM1")

For Visit 7, if the biotube is not transplanted on the same day as Visit 6 and the biotube is temporarily stored, it will be performed immediately before transplantation of the biotube. (For preservation of samples for histopathological evaluation, it will be performed if the amount of sample is sufficient)

[CRF description contents]

Total length, length, presence or absence of tears or holes (if present, length), presence or absence of thickness/extremely thin parts (if present, length), presence or absence of uneven parts (if present, length), presence or absence of leakage, tensile strength, pressure resistance, presence or absence of preservation of samples for histopathological evaluation, usable length, presence or absence of preservation of biotubes, evaluation date, presence or absence of abnormalities in appearance (decomposition, decay, abnormal odor, discoloration, etc.), presence or absence of preservation of samples for bacterial testing

(19) Biotube transplantation

[Survey items]

Information on biotube transplantation

[Survey period]

Visit 7

[CRF contents]

Whether or not biotube transplantation was performed, transplant date, confirmation date of transplant postponement, transplant date of transplant postponement, graft used, combination method, graft (biotube number), length of biotube used, autologous vein (site, length), artificial blood vessel (product name, length), pressure resistance, reason for transplant discontinuation, whether or not biotube was connected, date of connection, length of biotube after connection, whether or not it was pressure resistant (if not, reason), whether or not biotube was repaired

(20) Concomitant medications and concomitant therapies

Concomitant medications and concomitant therapies refer to all medications used or all treatments and procedures performed after obtaining consent. However, implantation of a test device and biotube implantation are excluded.

[Survey items]

Target medications, treatments and procedures

[Survey period]

From confirmation of eligibility to Visit 13 or discontinuation.

[CRF content]

Presence or absence of concomitant medications (if there are concomitant medications, the name of the drug (brand name or generic name), route of administration, single dose, frequency of administration, duration of administration, reason for administration), presence or absence of concomitant therapy (if there are

concomitant therapies, the name of the therapy, start date, end date, purpose of treatment)

(21) Adverse events

[Survey items]

Whether or not an adverse event occurred, and if so, information related to the adverse event

[Survey period]

From implantation of the study device until Visit 13 or discontinuation.

[CRF content]

See "7. Safety evaluation"

(22) Malfunctions

[Investigation items]

Whether or not a malfunction occurred, and if so, information related to the malfunction.

[Investigation period]

From Visit 2 (when the test device is implanted) to Visit 13 or cancellation.

Although the biotube is not a test device, in consideration of the characteristics of this clinical trial, malfunctions of the biotube will also be investigated. The investigation period for the biotube will be from Visit 6 (when the test device is removed) to Visit 13 or cancellation.

[CRF content]

See "7. Safety evaluation".

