3.2 Evaluation items

(1) Efficacy evaluation items

1) Primary evaluation items

Ability of forming biotubes using the test device

2) Secondary evaluation item

- ① Procedural success of implantation and removal of the test device
- ② Procedural success of bypass surgery, including distal anastomosis, using a biotube formed by the test device
- ③ Patency of the biotube at 12 weeks after implantation
- ④ Improvement of symptoms (improvement of ischemic pain, improvement of wounds)
- ⑤ Avoidance of major amputation
- ⑥ Rate of additional treatment during implantation of the study device and after implantation of the biotube
- ⑦ QOL during implantation of the test device and after implantation of the biotube
- ⑧ Bypass graft diameter after bypass surgery

[Rationale for setting]

First, it is necessary to confirm that the biotube formed using the test device can be used in bypass surgery and function as a substitute blood vessel. Next, it is necessary to examine whether the treatment is effective and whether symptoms can be improved to avoid amputation. Since symptoms usually improve in 12 weeks with bypass surgery using veins, it is necessary to observe the patient for up to 12 weeks.

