### (2) Procedural success of bypass surgery including peripheral anastomosis using a biotube formed by the test device

It will be visually evaluated whether the biotube can be sutured without damage or cutting using the same technique as a bypass surgery using a normal vein. It will be visually evaluated whether bleeding from the anastomosis site can be controlled, and there is no blood leakage, tearing, or swelling from the biotube wall. After releasing the vascular clamp, pulsatile blood flow is confirmed and the flow rate is measured with a flowmeter to evaluate peripheral revascularization. Note that "technical success" in this evaluation item refers to cases where bypass surgery was performed using only the biotube as a bypass graft (including cases where fragments of the biotube were joined together), and does not include cases where bypass surgery was performed by joining an autologous vein or an artificial blood vessel.

(3) Patency of the biotube at 12 weeks after implantation

During the follow-up period, blood flow in the biotube is evaluated by lower limb arterial echocardiography. If possible, the shape of the biotube is observed by lower limb CT angiography or lower limb arteriography to evaluate the presence or absence of abnormalities such as stenosis or swelling.

(4) Improvement of symptoms (improvement of ischemic pain, improvement of wounds)

The pain improvement rate, wound improvement rate, wound area reduction rate, and granulation formation rate are evaluated at the time of eligibility confirmation, at the time of biotube implantation, and 1, 4, 8, and 12 weeks after biotube implantation. In addition, the Wiffl score is also evaluated at the time of eligibility confirmation, and 1, 4, 8, and 12 weeks after biotube implantation.

(5) Avoidance of major amputation

The avoidance rate of major amputation of the target lower limb during the follow-up period will be examined.

(6) Implementation rate of additional treatment during implantation of the study device and after biotube implantation

The rate of revascularization other than bypass surgery using the biotube will be evaluated from implantation of the study device to the end of the follow-up period.

(7) QOL during implantation of the study device and after implantation of the biotube

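### The pain improvement rate in 8.2(4) has no standardised measure behind it: 6.5.1(2) records pain as present or absent plus unspecified details, with no graded scale and no attribution rule after bypass

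*Protocol*

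**What the plan says.** Protocol 3.2 lists as a secondary efficacy item "Improvement of symptoms (improvement of ischemic pain, improvement of wounds". Section 8.2(4) puts this into operation: "The pain improvement rate, wound improvement rate, wound area reduction rate, and granulation formation rate are evaluated at the time of eligibility confirmation", and again at biotube implantation and 1, 4, 8 and 12 weeks later. It gives no definition of improvement for pain and names no instrument.

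The data come from 6.5.1(2), Subjective and objective findings. The assessment method is "Confirm by examining the patient. Also, take a photograph of any wounds caused by the primary disease". The CRF contents open with "Presence or absence of subjective and objective findings and abnormalities associated with severe lower limb ischemia", then list the findings, including "presence or absence of pain, numbness, heat sensation, tenderness, swelling, wounds, exudate, ulcer/erosion formation", and go on to record "their details [including size (length and width) for wounds" among other things. So the form holds a yes/no entry for pain and some further detail, but a measurement is named for wounds only.

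The other source that touches on pain is the questionnaire in 6.5.1(16). Its post-implantation part covers "pain and itching at the implanted area, wound pain and improvement in walking, impact on daily life, other opinions", and it is given at "Visit 5, Visit 13, and at the time of discontinuation". Section 6.5.1(20) separately records every concomitant drug, with its dosing, duration and reason for use.

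**The concern.** An improvement rate needs a quantity that can improve by degrees, or a stated rule for when a change counts. For pain the protocol fixes neither at the point of collection. The only structured entry can show pain disappearing; it cannot show pain lessening. A subject whose severe rest pain falls to slight pain has the same entry, present, at both visits.

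The visits soon after bypass raise a second problem. A subject may then have incision pain as well as any remaining ischemic pain. The item is confined to findings linked to limb ischemia, but it gives the investigator no means of telling the two apart, such as location, type or a separate entry.

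What is at stake is whether this component of the symptom endpoint can be read at all. Section 1.2 places this trial ahead of a confirmatory one, so serial pain data collected here would be a natural input to planning that trial. A severity score not taken at the visit cannot be reconstructed later.

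**Working it through.** The protocol gives no pain rate, scale, threshold or pain-based sample size, so there is no figure to reproduce. The check sets the endpoint against the data that feed it.

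**1. Timing.** The six times in 8.2(4) correspond to eligibility confirmation and Visits 7, 10, 11, 12 and 13. Section 6.5.1(2) is scheduled at all six, so the visits needed already exist. The gap lies in what is recorded, not when.

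**2. Content, by item.**

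| Item | What is fixed | Times from 8.2(4) covered | Graded pain? |
|---|---|---|---|
| 6.5.1(2), pain | present/absent, plus unspecified details | all 6 | none named |
| 6.5.1(2), wounds | present/absent, length and width, photograph | all 6 | not applicable |
| 6.5.1(16), questionnaire | pain at the implanted area, wound pain, walking | 1 (week 12) | none named |
| 6.5.1(11), WIfI | wound, ischemia and foot infection scores | 5 (not at implantation) | no pain component |
| 6.5.1(20), medications | drug, dose, dates, reason | continuous | indirect only |

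Only the first row records limb pain serially. The questionnaire has no value at eligibility or at biotube implantation, so no change from baseline can be formed from it.

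**3. What the structured field can yield.** Write P = 1 for pain present and P = 0 for absent. From baseline to a later visit there are four patterns: 1 to 1, 1 to 0, 0 to 0 and 0 to 1. Only 1 to 0 can count as improvement. Any partial relief falls in 1 to 1, together with no change and with worsening. A subject with P = 0 at baseline cannot improve, so the denominator should be those with pain at baseline. Section 4.2 does not require pain for entry, so that number may be below 12.

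**4. What the details can yield.** They could record partial relief, but no content is prescribed. Turning them into a rate means grading free text across institutions after the event, with treatment known to all. Section 12.3 also allows efficacy evaluations and comments to have the CRF as their source when no primary record exists.

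**5. Sensitivity of the rate.** If all 12 subjects have pain at baseline and are assessed, one subject classified the other way moves the rate by 100/12 = 8.3 percentage points. If, as an assumption, only 6 have pain at baseline, the shift is 100/6 = 16.7 points. How many subjects would be affected cannot be derived from the protocol, which gives no pain data.

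**The case against.** The strongest reply is that the protocol collects more than a bare yes/no and leaves the derivation to the analysis plan. Much of this stands, and it rules out several stronger readings.

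- A reader might infer that pain is recorded purely as present or absent. The same CRF sentence goes on to ask for details, so that is not so.
- A reader might infer that partial relief will be scored as failure. Nothing says the rate is computed from the yes/no field, and section 9 defers detailed methods to the analysis plan. The result is conditional on that derivation.
- A reader might infer that ischemic and surgical pain are mixed by design. The item is limited to findings associated with limb ischemia, so a careful investigator would leave incision pain out, and the questionnaire asks about the implanted area separately. What is missing is an attribution rule; misattribution, chiefly at week 1, is a risk and not a literal consequence of the text.
- A reader might infer that relief due to new analgesics would go unseen. Section 6.5.1(20) captures those drugs with dose, duration and reason. The data exist, although 8.2(4) does not link them to pain.

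It is also fair that wound size, photographs, WIfI, ABI and SPP are collected serially, so the assessment of the limb does not rest on pain alone.

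The reply does not reach the core. An analysis plan can choose a responder rule, a baseline and a denominator; it cannot create a severity score that the CRF did not ask for.

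**Conclusion.** The point holds in limited form. Section 8.2(4) commits the trial to a serial pain improvement rate, while 6.5.1(2) supplies a yes/no entry and unspecified details, with no grade and no attribution rule. Two routes to the rate remain: a present-to-absent rule that treats partial relief as no improvement, or retrospective grading of free text in an open-label trial. Neither is a standardised measure of improvement in ischemic pain.

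The consequence is small. This is one component of one of eight secondary items; the primary endpoint in 8.1 is biotube formation, and the protocol rests no test, sample size or stopping rule on pain. No percentage of missed improvement is offered, because the protocol contains nothing from which to estimate it. The conclusion assumes that the CRF follows 6.5.1(2) as written and that no separate procedure adds a pain scale. On that footing it is a cheap improvement worth making, not a threat to the trial's main conclusion.

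**What to change.** In 6.5.1(2), add a 0-10 numeric rating of ischemic pain in the target limb at the visits already scheduled, recorded separately from incision pain. In 8.2(4), report the change in that score from the last value before bypass, with the eligibility value also shown, among subjects with pain at baseline. Present it alongside the analgesic use already captured under 6.5.1(20). If a rate is still wanted, state in advance what reduction counts as improvement.

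The cost is one extra CRF field and a short question at existing visits. Subjects already enrolled would lack the score for visits that have passed; they should be shown separately using the present/absent entry and not given a score from free text.

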## 6.5 Observation and inspection schedule

Observations and inspections will be carried out according to Table 6.5 below.

Table 6.5 Observation and inspection schedule

|                                             | Pre-observation period |                                       |                    | Test device implantation period       |                                  |                                  |                                                     |                                  | Post-observation period  |                              |                               |                                |                                 |                                 |                                  | Discontinuation                 |                         |
|---------------------------------------------|------------------------|---------------------------------------|--------------------|---------------------------------------|----------------------------------|----------------------------------|-----------------------------------------------------|----------------------------------|--------------------------|------------------------------|-------------------------------|--------------------------------|---------------------------------|---------------------------------|----------------------------------|---------------------------------|-------------------------|
|                                             | Obtaining consent      | Visit (V) 1
Confirming eligibility | Subject enrollment | V2
Implantation of the test device | V3
Removal of the break drain | V4
1 week after drain removal | V5
6 weeks after implantation of the test device | V6
Removal of the test device | V7
Biotebe transplant | V8
1 day after transplant | V9
3 days after transplant | V10
1 week after transplant | V11
4 weeks after transplant | V12
8 weeks after transplant | V13
12 weeks after transplant | Test device implantation period | Post-observation period |

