The results of a questionnaire conducted approximately 6 weeks after implantation of the study device will be used to evaluate the presence or absence of discomfort at the implantation site of the study device and the presence or absence of impact on daily life. In addition, the results of a questionnaire conducted at the end of the follow-up period will be used to evaluate the QOL after biotube implantation.

(8) Bypass graft diameter after bypass surgery

During the follow-up period, the diameter of the biotube used in the bypass surgery (including artificial blood vessels or autologous veins, if used) will be investigated and evaluated over time by lower limb arterial echocardiography.

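### The QOL questionnaire has a pre-implantation part and a walking-improvement item but is never given before implantation, and the timing of its first administration is contradictory

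*Protocol*

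**What the plan says.** Protocol 3.2 lists secondary item 7 as "QOL during implantation of the test device and after implantation of the biotube". Section 8.2 (7) evaluates it in two pieces. For the device period, "The results of a questionnaire conducted approximately 6 weeks after implantation of the study device will be used" to describe discomfort at the implantation site and effect on daily life. For the later period, "the results of a questionnaire conducted at the end of the follow-up period will be used to evaluate the QOL after biotube implantation".

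The form is specified in 6.5.1 (16). Its survey period is "Visit 5, Visit 13, and at the time of discontinuation", and the questionnaire row of Table 6.5 agrees. Table 6.5 defines Visit 5 as "6 weeks after implantation of the test device". The survey method in the same item reads differently: "A questionnaire survey was conducted on subjects after removal of the test device and 12 weeks after implantation of the biotube".

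The CRF contents have three parts:
- The first opens with "Before implantation of the test device (anxiety and expectations regarding the treatment of implanting the test device".
- The second concerns life with the device. It includes "impact on daily life and inconvenience, difference from imagination before implantation" and also feelings once the device is out.
- The third, read here as the period after the biotube bypass, covers the implanted area, wound pain, improvement in walking and daily life.

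**The concern.** The form has a section about the time before implantation but no administration at that time. It also asks for a judgement of improvement in walking without an earlier walking answer to compare it with. Both rest on the memory of subjects who, in an open-label trial, know how their implantation or operation went.

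The trial has no control group, so a subject's own earlier state is the only available comparator for a subject-reported outcome. Section 1.5.2 names recovery of walking and better activities of daily living among the expected benefits. Section 1.2 places this trial ahead of a confirmatory one. A baseline that is not asked for now cannot be recovered later.

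The conflict over when the first survey takes place adds to this. It decides whether the device-period answers describe a current state or a remembered one.

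**Working it through.** There is no figure in the plan to reproduce. The check compares the schedule with the content of the form.

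**1. Order of events (Table 6.5).** Visit 2 implantation; Visit 5 questionnaire; Visit 6 removal; Visit 7 bypass; Visit 13 questionnaire, 12 weeks after bypass. Scheduled administrations before implantation: 0. Scheduled administrations before bypass: 1 (Visit 5), if the Visit 5 timing governs.

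**2. Which items have a prospective earlier value.**

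| Item | Before implantation | Before bypass |
|---|---|---|
| Anxiety and expectations about the device | None; recalled at the first survey | Not applicable |
| Walking (subject-reported) | None | None |
| Daily life as affected by the limb | None | None; the Visit 5 item sits in the device part |
| Pain and wounds | Yes: 6.5.1 (2), eligibility and Visit 2; 8.2 (4), eligibility | Yes: 6.5.1 (2), Visits 5, 6 and 7; 8.2 (4), at biotube implantation |

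The findings listed in 6.5.1 (2) do not include walking, and no other item in 6.5.1 records it before Visit 13.

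**3. Length of recall.** Inputs: device in place 4 to 24 weeks (6.4.2 (1) and 6.4.4); temporary storage 0 to 4 weeks (6.4.2 (1)); Visit 13 at 12 weeks after bypass (Table 6.5).
- Pre-implantation part, Visit 5 timing: about 6 weeks.
- Pre-implantation part, after-removal timing: at least the time the device was in place, so 4 to 24 weeks or more.
- Visit 13, back to before bypass: 12 weeks.
- Visit 13, back to before implantation: device time + storage + 12. Shortest 4 + 0 + 12 = 16 weeks; longest 24 + 4 + 12 = 40 weeks.

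**4. Timing of the first survey.** The survey period in 6.5.1 (16), Table 6.5 and 8.2 (7) all put it about 6 weeks after implantation. The survey method in 6.5.1 (16) puts it after removal, which is Visit 6. In principle the device stays for 8 weeks or more (6.4.4), so at week 6 it is normally still in place and the item on feelings after removal cannot be answered. Removal between weeks 4 and 6 is allowed, and 6.4.2 (3) provides for removal and bypass on the same day. In such a subject, or under the after-removal wording, the first questionnaire can fall on or after the day of bypass, and the count of pre-bypass administrations drops from 1 to 0.

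**The case against.** The strongest reply is that item 7 is not defined as a change. Sections 3.2 and 8.2 (7) describe two periods, each from its own questionnaire, and the pre-implantation opinions are not among the things 8.2 (7) says it will evaluate. The trial is exploratory, with 12 cases, and its primary question is biotube formation. All of this stands. It limits the point to the value of the collected data and does not make the endpoint invalid.

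A reader might infer more than the protocol supports:
- **That nothing is asked before bypass.** Visit 5 is scheduled before Visits 6 and 7 and asks about daily life with the device.
- **That both halves of item 7 rest on recall.** With the device in place, the Visit 5 answers on discomfort and daily life describe a current state, and so do most of the Visit 13 items. Improvement in walking is the clear exception.
- **That pain and wounds lack a baseline.** They have one, under 6.5.1 (2) and 8.2 (4).
- **That all 12 subjects carry the Visit 13 gap.** Those who discontinue before bypass have no post-bypass period.

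A practical objection to a pre-bypass baseline is that removal and bypass may share a day, or that with storage the baseline may follow the removal operation by up to 4 weeks. The first case is met by asking before the removal operation. In the second, some effect of recovery from removal may remain in the answer.

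**Conclusion.** The point holds in limited form, as an inexpensive improvement to one secondary item.

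- The pre-implantation part is answered from memory, after about 6 weeks if Visit 5 governs and after 4 to 24 weeks or more if the after-removal wording governs.
- Subject-reported walking and limb-related daily life have no planned value before implantation or before bypass. Improvement in walking is therefore a single retrospective judgement, 12 weeks after bypass and 16 to 40 weeks after implantation.
- The timing of the first survey contradicts itself within 6.5.1 (16), and one item does not fit the Visit 5 timing.

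It would go too far to say that endpoint (7) cannot be evaluated. As defined, it can be described for each period once the timing is settled. What the data cannot give is a prospective change in walking or limb-related daily life. This rests on two readings: that the third part of the form refers to the time after bypass, and that the daily-life item in the second part refers to the device, as its placement indicates.

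**What to change.** 1. Give the pre-implantation part at Visit 1, or at Visit 2 before implantation.
2. Ask the walking and daily-life items in the same wording at Visit 1 or 2, again before bypass, and at Visit 13. Where removal and bypass fall on the same day, ask the pre-bypass set before the removal operation at Visit 6. Word the items as current state, referring to the target limb.
3. Keep endpoint (7) as defined in 8.2 (7), and report the within-subject change in these items descriptively beside it.
4. Reconcile the survey period and the survey method in 6.5.1 (16) with each other and with 8.2 (7) and Table 6.5. Move the item on feelings after removal to a scheduled visit after removal, and state what is done when removal comes before week 6.

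Cost: two short extra administrations for a subject who reaches bypass and one for a subject who stops earlier, all at visits that already take place. There are also added marks in the schedule tables and a small edit to the form. Subjects already past implantation when the change takes effect will still lack the earlier values, and the report should say so.
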